### Interventions

2.4

All participants enrolled in this trial will be antidepressant-naïve before enrollment. In China, traditional Chinese medicine is commonly used either alone or in combination with antidepressants for the treatment of depression. Therefore, this trial will adopt a stratified design according to whether paroxetine is initiated after enrollment. Before randomization, qualified psychiatrists at each study center will determine whether paroxetine is clinically indicated, based on clinical assessment and discussion with the participant. This decision will not be influenced by subsequent allocation to MSNP or placebo. Within each stratum, participants will be randomly assigned in a 1:1 ratio to receive either MSNP granules or placebo granules. Accordingly, this design will generate four treatment conditions: MSNP alone, placebo alone, MSNP plus paroxetine, and placebo plus paroxetine.

Participants in the combination-therapy stratum will receive paroxetine for 6 weeks. The dosing regimen will be 10 mg once daily on Days 1–2, followed by 20 mg once daily from Day 3 onward, taken orally as a whole tablet after breakfast. Dose adjustment will be allowed according to clinical response and tolerability, with a maximum daily dose of 50 mg. Paroxetine tablets will be supplied by Zhejiang Huahai Pharmaceutical Co., Ltd., with the National Medical Products Administration approval number H20031106.

Participants in the intervention group will receive MSNP granules, whereas those in the control group will receive placebo granules. The placebo granules will contain 5% MSNP granule material blended with pharmacologically inert excipients to mimic the appearance, odor, taste, and texture of MSNP. Both MSNP and placebo granules will be manufactured by Sichuan Neo-Green Pharmaceutical Technology Development Co., Ltd. In accordance with Good Manufacturing Practice requirements and relevant National Medical Products Administration regulations. The two formulations will be indistinguishable in appearance, texture, odor, and taste.

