According to this meta-analysis, in the non-paroxetine stratum, the expected total effective rates were 59.6% for MSNP alone and 37.0% for placebo alone, corresponding to a projected risk ratio of 1.61. In the paroxetine stratum, the expected total effective rates were 91.6% for MSNP plus paroxetine and 79.0% for placebo plus paroxetine, corresponding to a projected risk ratio of 1.16. Using the “Tests for Two Proportions” module in PASS version 21, with a two-sided alpha of 0.05, 80% power, equal allocation within each stratum, and an assumed dropout rate of 15%, the required sample sizes were 180 participants for the non-paroxetine stratum and 288 participants for the paroxetine stratum. Therefore, the final total sample size was set at 468 participants. In the non-paroxetine stratum, 90 participants will receive MSNP alone and 90 will receive placebo alone. In the paroxetine stratum, 144 participants will receive MSNP plus paroxetine and 144 will receive placebo plus paroxetine. Overall, 234 participants will receive MSNP-containing interventions (intervention group), and 234 participants will receive the corresponding placebo-containing control interventions (control group).

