### Statistical analysis

2.14

All efficacy analyses will be performed according to the intention-to-treat (ITT) principle in all randomized participants. Safety analyses will be conducted in all participants who initiate protocol-defined treatment. Missing outcome data will be handled using multiple imputation under the missing-at-random assumption.

The primary outcome (total effective rate) will be analyzed using a log-binomial regression model to estimate the adjusted RR and corresponding 95% confidence interval (CI) between the intervention and control groups. The model will include study center and concomitant paroxetine use as covariates. An interaction term between treatment group and paroxetine use will be included to assess the potential moderating effect of antidepressant co-administration on the intervention effect. Sensitivity analyses will include a predefined per-protocol (PP) analysis to assess the robustness of the findings. The PP population will include participants who complete the entire treatment course without major protocol violations and have available primary outcome data. Prespecified subgroup analyses will be performed according to baseline sex (male vs. female), age (≤55 vs. >55 years), depression severity (mild vs. moderate), NSCLC stage (I vs. II vs. III), and KPS score (70–80 vs. 90–100).

For other outcomes, repeated-measures continuous variables such as HAMD-17, PHQ-9, and GAD-7 scores will be analyzed using linear mixed-effects models to evaluate longitudinal changes from baseline between groups. The models will include group, time, group-by-time interaction, and baseline score as fixed effects, and participant and study center as random effects. For single-timepoint continuous variables such as inflammatory markers and neurotransmitters, between-group comparisons will be conducted using independent-samples t-tests or Mann–Whitney U tests, depending on data distribution. For time-to-event outcomes including PFS and OS, Cox proportional hazards models will be used to estimate hazard ratios and 95% CIs, adjusting for study center and paroxetine use. For categorical outcomes such as AE incidence and depression remission rate, group comparisons will be conducted using the chi-square test or Fisher’s exact test, as appropriate.

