## Discussion

3

This study is a nationwide, multicenter, randomized, double-blind, placebo-controlled clinical trial designed to systematically evaluate the efficacy, safety, and potential mechanisms of MSNP in the treatment of postoperative mild-to-moderate depression in patients with NSCLC. The trial is based on a rigorous methodological design, integrating multidimensional efficacy assessments and omics-based mechanistic analyses. It aims to address the current lack of high-quality clinical evidence for TCM interventions in depression.

Grounded in real-world clinical practice, this study adopts a design that ensures both scientific rigor and clinical applicability. First, it employs a strict randomized, double-blind, placebo-controlled design and is conducted collaboratively across nine research centers in different provinces of China, ensuring strong external validity and generalizability. Second, the study stratifies participants based on concomitant paroxetine use, with the aim of achieving two key objectives. The first is to evaluate the efficacy and safety of MSNP monotherapy as a viable alternative for patients who are unwilling or unable to tolerate antidepressants. The second is to explore the potential synergistic effects or mitigation of side effects when MSNP is combined with standard pharmacotherapy. This dual-scenario design enables a comprehensive appraisal of MSNP’s clinical value in personalized treatment strategies. In addition, the study includes multidimensional efficacy endpoints covering depression, anxiety, sleep disturbance, fear of recurrence, quality of life, and cancer survival. Multiple timepoint assessments are used to capture the psychological and physiological effects of MSNP in a comprehensive manner.

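### The treatment-by-paroxetine term compares two clinician-selected strata on a scale that favours a smaller effect with paroxetine, so it cannot show what co-administration does

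*Protocol article*

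**What the plan says.** Under Statistical analysis (2.14), the primary outcome is analysed with a "log-binomial regression model to estimate the adjusted RR". On covariates: "The model will include study center and concomitant paroxetine use as covariates". A treatment-by-paroxetine interaction is added, and its stated purpose is "to assess the potential moderating effect of antidepressant co-administration on the intervention effect".

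Under Interventions (2.4), the stratum is set before randomization: "qualified psychiatrists at each study center will determine whether paroxetine is clinically indicated, based on clinical assessment and discussion with the participant". What is randomized is MSNP against placebo: "Within each stratum, participants will be randomly assigned in a 1:1 ratio to receive either MSNP granules or placebo granules".

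Under Sample size estimation (2.9), the non-paroxetine stratum is planned at 59.6% against 37.0% (RR 1.61). For the other stratum, "the expected total effective rates were 91.6% for MSNP plus paroxetine and 79.0% for placebo plus paroxetine" (RR 1.16).

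The Discussion gives two reasons for stratifying. One is to evaluate MSNP alone as an option for patients who do not want or do not tolerate antidepressants. The other is to "explore the potential synergistic effects or mitigation of side effects when MSNP is combined with standard pharmacotherapy". The limitations paragraph does not mention that the strata are not randomized.

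**The concern.** The stated purpose makes paroxetine itself the moderator. The strata are formed by indication and patient preference, and they may differ in severity and in other ways that bear on response to MSNP. The model adjusts only for centre and stratum. An interaction would mix any effect of the drug with differences between the patients who were and were not started on it.

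The second difficulty is the scale. In a log-binomial model the interaction is a ratio of two risk ratios. When one stratum has a planned control response of 79%, its risk ratio has little room to rise. A ratio well below 1 then follows largely from the control rates, and a reader could take it as evidence that paroxetine weakens MSNP. At stake is what the trial may say about combined use, which is one of its two reasons for stratifying.

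**Working it through.** **Inputs.** From 2.9: rates 0.596 and 0.370 (no paroxetine), 0.916 and 0.790 (paroxetine); 90 and 144 patients per arm; two-sided alpha 0.05; power 80%; dropout 15%. Using 0.05 for the interaction test is an assumption, because 2.14 states that level for the primary outcome without naming the interaction.

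**The plan's own figures.** RR = 0.596/0.370 = 1.61 and 0.916/0.790 = 1.16, as stated. The two-proportion formula with pooled variance and no continuity correction gives 76 per arm without paroxetine; 76/0.85 = 89.4, so 90 per arm and 180 in total, as stated. With paroxetine it gives 123 per arm; 123/0.85 = 144.7, so 145 per arm and 290 in total, against 288 stated, which is close enough to confirm the inputs.

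**Ceiling.** Maximum RR = 1/control rate = 1/0.79 = 1.27. Matching an RR of 1.61 would need a response of 0.79 × 1.611 = 127%. Even 100% response on MSNP plus paroxetine gives a ratio of RRs of 1.266/1.611 = 0.79. The cap moves with the control rate: 1.43 at 70%, 1.33 at 75%, 1.18 at 85%. An RR of 1.61 becomes attainable only at about 62% or below.

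**The contrast on three scales, at the planning rates.**

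| Scale | No paroxetine | Paroxetine | Contrast |
|---|---|---|---|
| Risk ratio | 1.61 | 1.16 | ratio 0.72 |
| Risk difference | 22.6 points | 12.6 points | −10.0 points |
| Odds ratio | 2.51 | 2.90 | ratio 1.15 |

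**How often the RR interaction is significant.** The variance of the log ratio of RRs is the sum of (1 − p)/(np) over the four arms. With 90 and 144 per arm: 0.00753 + 0.01892 + 0.00064 + 0.00185 = 0.02894, so SE = 0.170. Then z = ln(0.720)/0.170 = −0.329/0.170 = −1.93, and the rejection probability is about 49%. A simulation of 200,000 trials also gave 49%, almost all towards a smaller RR with paroxetine. With 15% lost (76 and 122 per arm), SE = 0.185, z = −1.78 and the probability is about 43%.

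The same calculation on the risk-difference scale gives about 22% (20% after loss). On the odds scale it gives about 6% in both cases.

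**Identical odds ratios in both strata.** Hold the control rates at 37.0% and 79.0%. A common OR of 2.51 gives treated rates of 59.6% and 90.4% and a ratio of RRs of 1.145/1.611 = 0.71. A common OR of 2.90 gives 63.0% and 91.6% and a ratio of 0.68. The RR interaction is then significant in 52% (OR 2.51) to 63% (OR 2.90) of trials with all patients, and 45% to 56% after 15% loss. The overall range is about 45–63%, with no difference in effect on the odds scale.

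**The case against.** The strongest reply is that nothing here is improper as a description. The paroxetine decision precedes allocation and is unaffected by it, so the stratum is a legitimate baseline effect modifier, and a modifier need not be randomized. The RR is the primary measure, so an RR-scale interaction is coherent with it. The plan prints 1.61 and 1.16 together and sizes each stratum separately, so the difference is disclosed. Severity, a likely driver of indication, already has a prespecified subgroup analysis. All of this stands, and the term is valid as a statement of how the RR differs between strata. It does not rescue the words that attribute that difference to co-administration.

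A reader might go further and infer that a weaker effect with paroxetine would be a pure artefact. The documents do not support that. The planned risk difference also falls, by 10 points, so two of three scales agree that MSNP adds less where most patients already respond. Only the odds ratio points the other way, and only slightly.

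A reader might also infer that the protocol commits itself to reading this term as synergy. It does not. Synergy appears only in the Discussion, as something to explore, and is not tied to this term.

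Finally, replacing the RR test with an odds-scale test, or adding a HAMD-17-by-treatment term, is a debatable preference. At the planning rates the odds-scale test would reject in only about 6% of trials, and neither change would remove confounding by indication.

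**Conclusion.** The point holds in a limited form. The treatment-by-paroxetine term estimates heterogeneity of the MSNP effect between two patient groups selected by psychiatrist and participant, and the design gives no basis for attributing it to paroxetine. This part rests on the text alone.

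The scale problem is conditional on the planning rates. If they hold, a significant RR interaction is close to an even chance (49% with complete data, 43% after 15% loss), and it would occur at about 45–63% under identical odds ratios of 2.5–2.9. A lower control response with paroxetine would loosen the ceiling. The rejection figures use unadjusted large-sample tests without centre terms or imputation.

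Taken alone, a significant RR interaction would show neither antagonism nor absence of synergy. The randomized comparisons within strata and the sample size are unaffected.

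**What to change.** - In 2.14, restate the purpose of the term as describing heterogeneity of the MSNP effect between two clinician-selected strata.
- Report stratum-specific risk ratios, risk differences and odds ratios with confidence intervals. Beside the RR-scale interaction, give the additive-scale interaction, with the odds scale as supportive.
- State that no conclusion about moderation by, or synergy with, paroxetine will be drawn from this term.
- Add the non-randomized stratum to the limitations in the Discussion.
- Limit the monotherapy claim in the Discussion to antidepressant-naive patients for whom paroxetine was not started. Because 2.3.1 requires no previous antidepressant use, demonstrated intolerance is not represented.

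The RR-scale test can stay; an odds-scale replacement or a HAMD-17 interaction is optional. The cost is some wording, a few table rows and a weaker statement on synergy. Sample size and conduct do not change, and recruitment is not expected to start before June 2026.

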### Sample size estimation

2.9

Previous clinical studies have shown that SNP, either alone or in combination with antidepressants, may help alleviate depressive symptoms. For example, a randomized, double-blind, placebo-controlled trial in breast cancer patients with mild to moderate depression showed that SNP significantly reduced HAMD-24 scores compared with placebo, with a greater reduction in the SNP group than in the placebo group (4.46 ± 4.403 vs. 0.66 ± 4.463, *P* < 0.001) (Hong et al., 2026). Another randomized trial, in which effectiveness was defined as a ≥25% reduction in the HAMD-17 total score from baseline, showed that SNP combined with fluoxetine improved the total effective rate in adolescents with depression compared with fluoxetine alone (95.12% vs. 77.50%, *P* < 0.05) (Zhang et al., 2023). These studies provide specific clinical evidence supporting the potential antidepressant effects of SNP.

The sample size was calculated based on the primary outcome, namely, the total effective rate at the end of the 6-week treatment period. Considering that concomitant use of antidepressants may affect treatment response, a stratified design was adopted, and sample sizes were estimated separately for the two strata: participants without paroxetine use and participants with paroxetine use. Because individual clinical trials differed from the present study in population characteristics, disease context, and intervention setting, the formal assumptions for sample size estimation were not directly derived from a single clinical trial. Instead, they were primarily based on the pooled effect estimates from a previous meta-analysis of traditional Chinese medicine for depression, which provided more robust parameter estimates (Wang et al., 2019).

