### Randomization

2.11

A total of 468 participants will be enrolled from nine research centers, with 52 participants planned for each center. Randomization will be stratified by study center and by whether paroxetine is initiated after enrollment, with 20 participants in the non-paroxetine stratum and 32 participants in the paroxetine stratum at each center. Within each stratum, participants will be randomly assigned in a 1:1 ratio to receive either MSNP granules or placebo granules. The random allocation sequence will be generated by an independent statistician using computer software and restricted block randomization. Details of the block size and other restriction procedures will be kept in a separate confidential document unavailable to personnel responsible for enrollment or intervention assignment. The randomization sequence will correspond to sequentially numbered study medication codes. After eligibility confirmation and written informed consent, participants will receive the next available medication code according to their study center and paroxetine stratum.

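### The mixed models and the remission test leave out the paroxetine stratum used in randomisation, which makes these secondary analyses modestly conservative, and the pooled AE comparison cannot address the side-effect aim

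*Protocol article*

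**What the plan says.** All references are to the protocol article.

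- **Randomization:** "Randomization will be stratified by study center and by whether paroxetine is initiated after enrollment". Each centre is to enrol 20 participants without and 32 with paroxetine, allocated 1:1 within stratum.
- **Sample size estimation**, the reason for stratifying: "Considering that concomitant use of antidepressants may affect treatment response, a stratified design was adopted". For the stratum without paroxetine, "the expected total effective rates were 59.6% for MSNP alone and 37.0% for placebo alone". With paroxetine the planned rates are 91.6% and 79.0%.
- **Statistical analysis, primary outcome:** "The model will include study center and concomitant paroxetine use as covariates", plus a treatment-by-paroxetine interaction.
- **Statistical analysis, PFS and OS:** "Cox proportional hazards models will be used to estimate hazard ratios and 95% CIs, adjusting for study center and paroxetine use".
- **Statistical analysis, repeated scores:** "The models will include group, time, group-by-time interaction, and baseline score as fixed effects, and participant and study center as random effects". No paroxetine term appears.
- **Statistical analysis, remission and AEs:** "For categorical outcomes such as AE incidence and depression remission rate, group comparisons will be conducted using the chi-square test or Fisher’s exact test". No stratification is mentioned.
- **Discussion:** one of the two stated purposes of stratifying is to explore synergy, or mitigation of side effects, when MSNP is added to standard drug treatment.

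**The concern.** The plan treats paroxetine as important enough to stratify on, and adjusts the response and survival models for it. It then leaves it out of the depression scores, the outcomes that an antidepressant targets most directly. This is not detail left to a SAP: the article lists the model terms and names the tests.

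When a balanced prognostic factor is left out, its between-stratum variance stays in the error term although the design has removed it from the treatment comparison. Standard errors are then too large, intervals over-cover, tests fall below their nominal level and some power is lost.

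A separate issue concerns safety. A pooled AE comparison mixes participants on paroxetine with participants who never take it, so it cannot show whether MSNP mitigates paroxetine's side effects.

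**Working it through.** **Inputs from the document.** Strata of 180 and 288, so the weights are 180/468 = 0.385 and 288/468 = 0.615. There are 234 per arm (90 + 144). Planned response, MSNP vs placebo: 59.6% vs 37.0% without paroxetine, 91.6% vs 79.0% with it. **Not in the document:** HAMD-17 SDs by stratum, remission rates and AE rates. These are assumed over ranges below.

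**1. The plan's own figure.** Two-proportion formula, pooled variance, no continuity correction, two-sided 0.05, 80% power, then division by 0.85 for dropout:
- Without paroxetine: 76 per arm, 76/0.85 → 90, total 180, as stated.
- With paroxetine: 123 per arm, 123/0.85 → 145, total 290 against 288 stated. The difference is immaterial here.

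The planning rates are therefore read correctly.

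**2. How large the planned stratum gap is.** Control arms: 79.0 − 37.0 = 42.0 points. MSNP arms: 91.6 − 59.6 = 32.0 points. The planned treatment effects are 22.6 and 12.6 points.

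**3. Binary outcome at the plan's response rates.**
- Overall rates: control 0.385×0.370 + 0.615×0.790 = 0.628; MSNP 0.385×0.596 + 0.615×0.916 = 0.793.
- Unstratified variance sum: 0.628×0.372 + 0.793×0.207 = 0.3977 (from unrounded rates).
- Stratified variance sum: 0.385×(0.370×0.630 + 0.596×0.404) + 0.615×(0.790×0.210 + 0.916×0.084) = 0.3317.
- SE = √(sum/234): 0.0412 unstratified, 0.0377 stratified, ratio 1.095.
- 95% half-width: 8.1 against 7.4 points, so the unstratified interval is 9.5% too wide.

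**4. Type I error and power.** With 37%/79% in both arms, the closed form gives a plain chi-square test a true level of 0.0306. Simulation (200,000 runs, 90 and 144 per arm) gives 0.031 for chi-square and 0.050 for Cochran-Mantel-Haenszel (CMH). For an assumed smaller effect (49%/86% vs 37%/79%), power is 54.7% for chi-square and 61.8% for CMH.

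**5. Remission, assumed rates.** Control rates are without/with paroxetine; MSNP is 10 points higher for the width column.

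| Control remission | Excess CI width | True level of chi-square |
|---|---|---|
| 30% / 40% | 0.5% | 0.049 |
| 20% / 50% | 5% | 0.040 |
| 15% / 60% | 11% | 0.029 |

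A still wider assumed gap, 10%/60%, would give about 15%.

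**6. Mixed models.** Let d be the stratum difference in residual SDs. For a single time point the SE ratio is √(1 + 0.385×0.615×d²), which gives 3%, 7% and 13% excess at d = 0.5, 0.8 and 1.1. A repeated-measures simulation (60 runs per setting, four visits, gap building to full size by week 6, centre fitted as fixed) gives a week-6 SE that is 2%, 4.5% and 9% too large.

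**7. AEs.** At assumed rates of 5%/15% the excess width is about 1% and the true level 0.047, which is negligible. The dilution is not: 180/468 = 38.5% of the pooled sample takes no paroxetine and carries no information on mitigation of its side effects.

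**The case against.** The strongest reply is that little harm follows. Allocation is 1:1 within strata, so the treatment difference is not biased and false positives do not increase. The outcomes concerned are secondary, declared exploratory, or safety, and the primary analysis already adjusts for paroxetine. All of that stands, and it limits the weight of the point. It does not explain why PFS and OS, which are also secondary, are adjusted while depression scores are not.

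Several stronger readings are tempting, but the document does not support them:

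- **Paroxetine as the strongest predictor.** The plan says only that antidepressants may affect response, and it quantifies no other predictor. Paroxetine is started on clinical indication, so the strata may also differ in severity, and baseline score may absorb part of the gap.
- **SE inflated by 14%, with a true error of 2.5%.** This converts 37% vs 79% to a latent shift of 1.14 SD at a single time point: √(1 + 0.385×0.615×1.14²) = 1.14. It is an upper-end figure. The repeated-measures simulation gives 2–9%, or a true level of about 4.6% down to 3.3%.
- **A loss equal to about 20% more patients** (1/0.834, where 0.834 = 0.3317/0.3977). This holds for a 25% HAMD-17 reduction at the planned rates. It does not carry over to remission (HAMD-17 ≤7) or to AEs.
- **Intervals too wide for remission and AEs.** The plan promises tests for these outcomes, not intervals. The direct consequence is a conservative p-value.
- **No analysis at all for the side-effect aim.** The safety section gives particular attention to listed paroxetine reactions, and by-stratum tables are not excluded. What can be said is that the only stated AE comparison is not split by stratum.

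**Conclusion.** The point holds as an inconsistency with a modest, conservative cost. The mixed models and the remission test ignore a randomisation stratum that the plan's own rates mark as likely prognostic.

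The 9.5% and 0.03 figures rest on the plan's response rates. The mixed-model range assumes gaps of 0.5–1.1 residual SD, and the remission range assumes control rates from 30%/40% to 15%/60%. If the true gaps are small, the loss is close to nil.

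For AEs the reason to act is not precision. The pooled comparison does not match the stated aim of exploring mitigation of side effects. Correcting all of this is a worthwhile improvement and not a condition for the trial's validity.

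**What to change.** - **Mixed models:** add the paroxetine stratum as randomised, and stratum-by-time, as fixed effects for all repeated scores.
- **Remission:** use CMH over the strata, or a main-effects risk-ratio model adjusted for paroxetine, centre and baseline HAMD-17. Do not copy the primary model unchanged: its treatment-by-paroxetine interaction would leave no single overall risk ratio. Keep any interaction in a separate model.
- **AEs:** compare the listed paroxetine reactions between arms within the paroxetine stratum, in addition to the overall comparison.

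The cost is wording in the protocol as well as the SAP, since the protocol itself lists the model terms. No extra participants, visits or data are needed. Recruitment was anticipated to begin only in June 2026, so the change can be prespecified before outcome data are seen.

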In most clinical settings in China, pharmacological treatments remain the most common approach. Selective serotonin reuptake inhibitors (SSRIs) are the most widely used first-line antidepressants, with representatives such as paroxetine, fluoxetine, sertraline, citalopram, and escitalopram. SSRIs work by selectively blocking the serotonin transporter on the presynaptic membrane, thereby increasing serotonin levels in the synaptic cleft and improving depressive symptoms (Seiger et al., 2021). Notably, some studies have suggested that SSRIs may possess potential antitumor properties, which has attracted interest in their use among cancer patients (Özkaya Gül and Aydemir, 2025). However, treatment response to SSRIs remains incomplete. When a 50% reduction in the 17-item Hamilton Depression Rating Scale (HAMD-17) is used as the response criterion, the response rate to SSRIs is approximately 60% (Zhao et al., 2019). In addition, common adverse effects of SSRIs, including gastrointestinal discomfort, dizziness, sleep disturbance, weight gain, and sexual dysfunction, may compromise treatment adherence and tolerability (Edinoff et al., 2022).

Against this background, traditional Chinese medicine (TCM) has gained increasing attention as a safe, cost-effective, low-toxicity, and multi-target intervention for cancer-related depression. According to TCM theory, liver qi stagnation is key to the pathogenesis of depression, and the treatment principle focuses on soothing the liver and regulating qi (Chen et al., 2021). A meta-analysis has shown that TCM formulas based on this therapeutic principle, whether used alone or in combination with antidepressants or psychotherapy, can help alleviate depressive symptoms in cancer patients (Wang et al., 2019). However, the analysis also highlighted significant methodological flaws in the included trials, such as insufficient reporting, high risk of bias, and substantial heterogeneity, suggesting the need for further high-quality studies to validate these findings.

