
#### Exploratory outcomes

2.6.3

To systematically investigate the potential mechanisms of action of MSNP granules, biological samples will be collected for analysis. At each study center, the first 20 participants enrolled in each stratification group (with or without concomitant paroxetine use) will be selected, yielding a total of 40 participants per center for mechanistic assessments. Peripheral blood and fecal samples will be obtained at baseline and at Week 6. Fasting venous blood samples will be drawn from the antecubital vein between 8:00 and 10:00 a.m. After standing at room temperature for 1 h, the samples will be centrifuged at 3,000 rpm for 1 min to obtain the supernatant. This will be followed by a second centrifugation at 12,000 rpm for 10 min at 4 °C to isolate serum (Wang et al., 2022). Fecal samples will be collected immediately after morning defecation using sterile containers. All serum and fecal specimens will be stored at −80 °C until further analysis. The following mechanistic indicators will be assessed:Serum inflammatory markers, including interleukin-1β (IL-1β), interleukin-6 (IL-6), C-reactive protein (CRP), and tumor necrosis factor-α (TNF-α), measured using enzyme-linked immunosorbent assay (ELISA).Serum hormones associated with the HPA axis, including adrenocorticotropic hormone (ACTH), corticotropin-releasing hormone (CRH), and cortisol (CORT), also measured using ELISA.Serum neurotransmitters, including dopamine (DA), norepinephrine (NE), and 5-hydroxytryptamine (5-HT), quantified using high-performance liquid chromatography with electrochemical detection.Serum BDNF, measured using ELISA.Serum metabolomic profiles, analyzed through non-targeted liquid chromatography–mass spectrometry.Gut microbiota composition, assessed via 16S rRNA gene sequencing.

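### Biomarkers sampled at baseline and Week 6 are labelled single-timepoint and compared with covariate-free tests, which costs precision in the exploratory mechanistic outcomes

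*Protocol article*

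**What the plan says.** Four places in the protocol article bear on this point.

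- **Section 2.6.3 (Exploratory outcomes), timing:** "Peripheral blood and fecal samples will be obtained at baseline and at Week 6". The serum inflammatory markers and neurotransmitters are among the assays listed for these samples.
- **Section 2.6.3, who is sampled:** "the first 20 participants enrolled in each stratification group (with or without concomitant paroxetine use) will be selected". This rule applies at every site, so the mechanistic subset is 20 + 20 = 40 at each.
- **Section 2.11 (Randomization):** "Randomization will be stratified by study center and by whether paroxetine is initiated after enrollment".
- **Section 2.14 (Statistical analysis), biomarkers:** "For single-timepoint continuous variables such as inflammatory markers and neurotransmitters, between-group comparisons will be conducted using independent-samples t-tests". The full choice is "independent-samples t-tests or Mann–Whitney U tests, depending on data distribution". No baseline, center or paroxetine term is named.

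Section 2.14 treats other outcomes differently. For the repeated scales: "The models will include group, time, group-by-time interaction, and baseline score as fixed effects, and participant and study center as random effects". The primary log-binomial model and the Cox models for PFS and OS adjust for center and paroxetine use.

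**The concern.** The two sections describe the same data differently. Section 2.6.3 gives every sampled participant two measurements of each marker, while section 2.14 gives the same markers as examples of variables measured once and picks the test on that footing. An independent-samples t-test or a Mann–Whitney U test takes no covariates, so neither the baseline value nor the randomization strata can enter.

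Mechanism is a stated aim of the trial, and the baseline samples are already planned. Leaving them out, or using them inefficiently, widens the confidence intervals on every marker. The text also does not say whether the tested quantity is the Week 6 value or the change from baseline, so two analysts could follow section 2.14 and report different results.

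**Working it through.** **Inputs from the protocol article**
- Sampled: 20 per paroxetine stratum per center, so 40 per center; 9 × 40 = 360, with 180 in each paroxetine stratum.
- Allocation is 1:1 within strata, so about 180 per arm.
- Dropout 15% (section 2.9, assumed there for the primary outcome): 360 × 0.85 = 306, or 153 per arm.
- No sample size or power is stated for the biomarkers, so there is no planned figure to reproduce. The total of 468 belongs to the primary outcome.

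**Assumptions, not in the article**
- Baseline-to-Week 6 correlation r: 0.3 to 0.7.
- Equal SD at both visits, and the same r in both arms.
- Difference in marker level between paroxetine strata: 0.2 to 0.8 SD.

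**Step 1. Variance of the treatment effect, relative to a t-test on Week 6 alone**

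Week 6 only = 1; change score = 2(1 − r); ANCOVA = 1 − r².

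| r | Change score | ANCOVA | ANCOVA reduction against Week 6 only | Change score / ANCOVA |
|---|---|---|---|---|
| 0.3 | 1.40 | 0.91 | 9% | 1.40/0.91 = 1.54 |
| 0.5 | 1.00 | 0.75 | 25% | 1.00/0.75 = 1.33 |
| 0.6 | 0.80 | 0.64 | 36% | 0.80/0.64 = 1.25 |
| 0.7 | 0.60 | 0.51 | 49% | 0.60/0.51 = 1.18 |

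The change score is less precise than ANCOVA throughout this range, and less precise than Week 6 alone when r is below 0.5.

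**Step 2. Equivalent number of participants at r = 0.6**

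360 / 0.64 ≈ 563. After 15% dropout, 306 / 0.64 ≈ 478. So ANCOVA on the sampled participants carries the information that a Week 6-only t-test would need about 563 (or 478) participants to match.

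**Step 3. Detectable difference at 80% power, two-sided 0.05**

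(1.960 + 0.842) × √(2/n) × √(relative variance), in SD units.

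| | Week 6 only | ANCOVA, r = 0.3 | ANCOVA, r = 0.5 | ANCOVA, r = 0.7 |
|---|---|---|---|---|
| 180 per arm | 0.295 | 0.282 | 0.256 | 0.211 |
| 153 per arm | 0.320 | 0.306 | 0.277 | 0.229 |

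**Step 4. Ignoring the paroxetine stratum**

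With the subset split equally, a between-stratum difference of s SD multiplies the outcome variance by 1 + s²/4.
- s = 0.2: 1.01 (1% more)
- s = 0.5: 1.06 (6% more)
- s = 0.8: 1.16 (16% more)

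**The case against.** The strongest defence is that single-timepoint may mean one post-baseline assessment, in contrast to the scales rated at several post-baseline visits, and that a change from baseline may be what is tested. This stands in part: section 2.14 does not settle the tested quantity, so a reader who infers that the baseline is certainly discarded goes beyond the text. The defence does not rescue the method. A change score is still less efficient than ANCOVA, and the strata stay out under either reading.

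Three other stronger readings are tempting and not supported.

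- **Bias.** A reader might infer that baseline imbalance or paroxetine use distorts the comparison. Allocation is 1:1 within center and paroxetine stratum, so an unadjusted comparison is not systematically biased, and ignoring the strata tends to make it conservative. Chance baseline imbalance is part of the variance counted above, not a further harm.
- **A known paroxetine effect on the measured serotonin.** The Background says "SSRIs work by selectively blocking the serotonin transporter on the presynaptic membrane", which concerns the synapse. The trial measures serum 5-HT, and the article gives no figure for paroxetine's effect on that. The stratum gain is therefore conditional, and it is negligible if the strata differ little.
- **No effect estimate from Mann–Whitney.** A shift or probability estimate can accompany that test, and such reporting detail is commonly left to an analysis plan. Choosing the test by the observed distribution is a secondary point: it leaves open until the data are seen whether means or ranks are compared.

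It is also fair to say that these outcomes are exploratory and carry no stated power or decision rule.

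**Conclusion.** The point holds as a contradiction between sections 2.6.3 and 2.14 and as an inefficient choice of analysis. The consequence is lost precision in exploratory mechanistic outcomes; the primary analysis, which already adjusts for center and paroxetine, is unaffected. The size depends on an assumed correlation: over r of 0.3 to 0.7 the excess variance is modest at the low end if Week 6 alone is tested, and largest at the low end if change is tested. The stratum contribution rests on a second assumption, the distance between strata, and may be trivial. What does not depend on any assumption is that the label is wrong, the tested quantity is not stated, and the named tests leave out the factors used to stratify randomization.

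**What to change.** In section 2.14, delete the single-timepoint label for these markers and state that each is analysed by ANCOVA: Week 6 value on treatment, baseline value, randomized paroxetine stratum and center. Log-transform skewed markers, with the baseline on the same scale. Report the adjusted mean difference with its 95% CI, or the ratio of geometric means for log-transformed markers. This replaces the distribution-dependent choice between two tests and settles which quantity is compared.

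The cost is a rewritten sentence in the protocol and the matching text in the analysis plan. No extra samples, visits or participants are needed, because the baseline samples are already scheduled.
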